During the study, the algorithms in both the control and experimental conditions will provide real-time prediction to subjects whether they likely have an active SARS-CoV-2 infection. Individuals with a suspected SARS-CoV-2 infection based on these algorithms will be encouraged to get tested using the existing testing infrastructure in the Netherlands provided by the Municipal Health services (GGD). At the moment of writing, the GGD offers free SARS-CoV-2 polymerase chain reaction (PCR) and antigen testing services. While in this protocol tests to confirm current SARS-CoV-2 infection are described as PCR and/or antigen tests, results from other validated testing methods used by the GGD will also be documented and processed in the same way, should the GGD choose to expand the type of tests being used to detect SARS-CoV-2 infection in Dutch residents. Subjects who are thought to have an SARS-CoV-2 infection according to the algorithm of the control or experimental condition, but are rejected for testing by the GGD, will be advised to use self-sampling kits provided by the study team which they can send to the central laboratory for testing. A reason for such rejection by the GGD may include not (yet) having overt symptoms of a respiratory tract infection plus not having any evidence (such as a GGD or CoronaMelder app notification) of having been in close contact with someone who tested SARS-CoV-2-positive. In addition, fingerstick capillary blood samples will be collected from COVID-RED subjects at baseline, after the Learning Phase (if applicable) and after the completion of each period. Samples collected after the Learning Phase and the completion of Period 2 will be tested for SARS-CoV-2 antibodies to determine whether the subject had a previous SARS-CoV-2 infection prior to the study or during the test periods (which was not detected through real-time SARS-CoV-2 infection testing). Baseline samples of subjects will only be analysed if the sample collected at the end of the Learning Phase is positive for SARS-CoV-2 antibodies or if the subject entered the study at the end of the recruitment Period. Samples of subjects collected at the end of Period 1 will only be analysed if the sample collected at the end of Period 2 is positive for SARS-CoV-2 antibodies.

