### 2.2 Secondary Objective(s):

1. To assess the health economic utilization of a wearable device and mobile application as measured by endpoints such as:
  - a. Number of tests for suspected SARS-CoV-2 infections
  - b. Number of hospitalizations
  - c. Number of ICU events
  - d. Number of days requiring breathing support (e.g. oxygen and/or ventilation)
2. To determine the incidence of SARS-CoV-2 infection during the study
3. Identify which features of the Ava bracelet and Daily Symptom Diary are the most predictive features
4. Assess the independent predictiveness of an algorithm derived from physiological data gathered by the Ava bracelet in addition to self-reported daily symptom data
5. To assess the time from algorithm indication to symptom onset in the subject
6. To assess the time from algorithm indication to testing of the subject
7. To determine how taking antipyretic medication affects physiological parameters among subjects using the Ava bracelet and Daily Symptom Diary
8. To determine how self-reported vaccinations cause changes in biophysical parameters from subject's given baseline measurements
9. To correlate the longitudinal symptoms reported by study subjects confirmed to have COVID-19 with changes over time in their physiological data
10. To characterise longitudinal symptoms and recovery dynamics reported by the study subjects to the presence or absence of lab-confirmed SARS-CoV-2 infection
11. To assess the adherence to daily symptom diary completion and Ava bracelet wearing and synchronising over time

12. To determine the time necessary to establish baseline physiological parameters per subject in the Learning Phase of the study
13. To determine if retrospective identification of the moment of potential SARS-CoV-2 infection is possible for subjects who are seropositive at the end of a period but were negative at baseline and did not receive an alert to get tested during the study
14. To determine the rate of breakthrough and asymptomatic COVID-19 infections among vaccinated individuals
15. To assess the influence of self-reported COVID-19 vaccinations on compliance to study procedures

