### 3.3 Implementation and development of algorithms

For both the control and experimental conditions, separate algorithms will be applied. For the control condition, an algorithm meant to predict potential active SARS-CoV-2 infections will be applied that incorporates deterministic expert-based rules regarding the presence of SARS-CoV-2 symptoms defined by the Dutch national institute for public health and the environment ‘Rijksinstituut voor Volksgezondheid en Milieu’ (RIVM) guidelines (at the time of writing these include: common cold symptoms [such as a nasal congestion, runny nose, sneezing, sore throat], coughing, shortness of breath, elevated temperature or fever, and sudden loss of smell and/or taste [without nasal congestion]). Any subject that experiences any of the above symptoms will be advised to get tested. For the experimental condition, a machine learning algorithm developed for the same purpose based on both symptom and confounder data as well as physiological parameters collected through the Ava bracelet will be applied on data collected during the study from the Daily Symptom Diary and the Ava bracelet. Both algorithms will give recommendations to the subjects whether they should get tested for SARS-CoV-2 infection. For the algorithm in the experimental condition to give a recommendation based on physiological data, it is first required to establish a baseline per subject of their “normal” physiological patterns. The period of time in which this baseline is determined is referred to as “baselining”. This will take place when subjects enter the study and will not be repeated within each period of the crossover portion of the trial. As soon as a stable baseline has been determined for all measured physiological parameters, the algorithm can start detecting when there are significant deviations from this baseline. For the

remainder of the Learning Phase the experimental condition algorithm will be applied for subjects that are part of this Phase. In Period 1 and 2, data from only the Daily Symptom Diary (control condition) or both the Diary and the bracelet (experimental condition) will be used to inform the algorithms that give indications to the subjects whether they should seek testing.

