- Time between first recommendation for testing and GGD SARS-CoV-2 test (stratified for antigen or PCR test if applicable)
- Time between first recommendation for testing and provided PCR SARS-CoV-2 test
- Time between first recommendation for testing and GGD SARS-CoV-2 test result (stratified for antigen or PCR test if applicable)

- Time between first recommendation for testing and Central laboratory SARS-CoV-2 test result

*COVID-19 Vaccination (collected during baseline and throughout the study through bi-weekly surveys in COVID-RED web portal)*

- Number of subjects who received a first and second (where relevant) dose of a COVID-19 vaccination stratified by manufacturer of the vaccine
- Time between first and second (where relevant) dose of the vaccine

*Behaviour (collected throughout the study through bi-weekly surveys in COVID-RED web portal):*

- Number of behavioural changes
- Behavioural changes made and reasons
- Number of behavioural changes (partly) due to the app or wearable
- Behavioural changes (partly) due to the app or wearable and reasons

*Daily Symptom Diary data (collected daily with Ava COVID-RED app)*

- Number and duration of each contiguous reported symptom:
  - Head:
    - Confusion
    - Difficulty concentrating
    - Dizziness
    - Fever
    - Headache
  - Nose and mouth:
    - Bluish lips or face
    - Loss of smell
    - Loss of taste
    - Nasal congestion or runny nose
  - Throat and sternum:
    - Nausea
    - Sore throat
    - Vomiting
  - Chest:
    - Chest tightness, pain or pressure
    - Dry cough

- Shortness of breath or difficulty breathing
- Lower back:
  - Chills or excessive sweating
  - Fatigue
  - Muscle or body aches
  - Skin impurities
- Abdomen:
  - Abdominal pain or cramping
  - Diarrhoea
  - Stomach ache
- General malaise
- No symptoms to report
- Average oral temperature and number/percentage of daily deviations above 38 degrees (Celsius), when collected
- Time between first algorithm indication for testing and symptom onset

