#### **8.4.12 Testing for presence of SARS-CoV-2 virus**

Subjects will receive specific instructions at the start of the study to always contact the GGD for SARS-CoV-2 virus testing when receiving a red-light indicator and only request for self-sampling kits for the central laboratory PCR testing service when turned down for testing by the GGD in line with the criteria applicable at that moment in time.

If subjects cannot be tested through the GGD because they do not qualify as per the current RIVM testing guidelines, they will be instructed to contact the study team and request a self-sampling PCR kit. The kit will be sent to them as soon as possible including instructions. Subjects will be instructed to take the sample and use the pre-addressed medical envelope with prepaid postage to send the sample to the central laboratory within 24 hours. The samples will be processed and stored at the central laboratory on the day of receipt. Results will be communicated back to the subjects and any positive results will be reported to the GGD.

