### 10.5 Analysis of Secondary Endpoint(s)

Secondary study endpoints mentioned in section 8.1.2 will be analysed and compared within the Intention-to-treat, Efficacy analysis and Partial compliance sets within each period. Where deemed relevant, analyses will also be executed within selected subsets of these analysis sets. Specific subsets will be listed within the Statistical Analysis Plan. Results will be presented in tables where possible. Where percentages are to be calculated, the number of subjects in the condition within the specified analysis (sub)set will be used as the denominator.

Where assumptions are met, Cochran-Mantel-Haenszel tests stratified by the risk strata will be performed in each period for multiple secondary endpoints, including:

- The number and percentage of subjects that obtained a red-light indicator by the applied algorithm at least once.
- The number and percentage of subjects with at least one positive SARS-CoV-2 virus test result during follow-up.

- The number and percentage of subjects that donated a blood sample for a SARS-CoV-2 antibody test at baseline, after the Learning Phase and after both periods.
- The number and percentage of subjects with a positive SARS-CoV-2 antibody test at baseline, after the Learning Phase and after both periods.
- The number and percentage of subjects with at least one positive SARS-CoV-2 virus test result during each period OR a positive SARS-CoV-2 antibody test result within those periods.
- The number and percentage of subjects without a positive SARS-CoV-2 virus test result during each period AND a negative SARS-CoV-2 antibody test result within those periods.
- The number and percentage of subjects that have reported experiencing each of the symptoms listed in the Ava COVID-RED app at least for one day during the study.
- The number and percentage of subjects that have reported experiencing each of the symptoms corresponding by the RIVM guidelines at least for one day during the study.
- The number of subjects who reported a positive SARS-CoV-2 virus test during the study and the percentage of subjects who reported a positive SARS-CoV-2 virus test during the study, with the number of subjects ever receiving a PCR test during the study as the denominator.

Where assumptions are met, t-tests will be performed in each period for multiple secondary endpoints, including:

- The average and median number of times a single subject obtained a red-light indicator by the applied algorithm.

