- The average and median number of continuous days that each symptom in the Ava COVID-RED app was reported to be experienced.
- The average and median number of continuous days that each symptom corresponding to the RIVM guidelines was reported to be experienced.
- The average (and variance) number of days between a red-light indicator of the applied algorithm and the SARS-CoV-2 virus test result, stratified for tests done via the GGD and central laboratory, and also stratified for testing methodology.
- The average (and variance) number of days between a red-light indicator of the applied algorithm and the taking of a SARS-CoV-2 virus test, stratified for tests done via the GGD and central laboratory, and also stratified for testing methodology.

- Number of total SARS-CoV-2 virus tests taken by subjects, stratified for tests taken by GGD and/or central laboratory, and also stratified by testing methodology if applicable (PCR vs. antigen tests).
- The number of total positive SARS-CoV-2 virus tests and percentage of positive tests, with the number of total tests within the study taken as a denominator. This will also be stratified for the different testing methodologies if applicable.
- Average and median duration of Ava bracelet and/or Ava COVID-RED app use (number of days between first day of use and last day of use)
- Compliance rate: percentage of days (as compared to duration of use) that Ava bracelet data was synced to Ava COVID-RED app or symptoms were entered. Upon inspection of the data, other modes (like Poisson regression) will also be considered.

For other relevant endpoints (e.g. survival status of subjects at end of follow-up) appropriate statistical methods (e.g. survival analysis) will be used. Further details will be indicated within a separate statistical analysis plan.

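### The red-light-to-test comparison uses only observed delays, split by test site, so it can show no difference although fewer experimental alerts lead to a timely test

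*Protocol*

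**What the plan says.** Section 2.2, item 6 sets the objective: "To assess the time from algorithm indication to testing of the subject". It names no test site.

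Section 10.5 turns this into an average (and variance) of days from a red-light "indicator of the applied algorithm and the taking of a SARS-CoV-2 virus test, stratified for tests done via the GGD and central laboratory", with a further split by test method. The item stands in a list introduced by "Where assumptions are met, t-tests will be performed in each period for multiple secondary endpoints, including".

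Section 8.1.2 defines the intervals per route, as separate endpoints: "Time between first recommendation for testing and GGD SARS-CoV-2 test (stratified for antigen or PCR test if applicable") and "Time between first recommendation for testing and provided PCR SARS-CoV-2 test".

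On how a subject reaches one route or the other:

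- Section 3.3 bases the control algorithm on symptoms from the national (RIVM) list: "Any subject that experiences any of the above symptoms will be advised to get tested". Section 3.5 says that these same symptoms qualify for GGD testing.
- Section 1.4, on GGD refusals: "A reason for such rejection by the GGD may include not (yet) having overt symptoms of a respiratory tract infection", when there is also no evidence of close contact with a case.
- Section 8.4.12 describes what follows: "If subjects cannot be tested through the GGD because they do not qualify as per the current RIVM testing guidelines", they contact the study team, request a kit, receive it by post, take the sample and mail it to the central laboratory.

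**The concern.** A mean delay exists only for an alert that was followed by a test. Testing is left to the subject (Appendix 1, note 2), and the red light only suggests that the subject consider it (Section 3.4), so some alerts will have no delay to average.

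The split by site adds a second selection. Bracelet alerts without symptoms occur only when bracelet data feed the algorithm, and these are the alerts most likely to be sent on to the kit route. Being tested, and where, are both events after randomisation that the condition can change. Comparing delays among testers within a site holds fixed two of the ways in which the experimental condition could alter time to testing.

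At stake is the answer to one secondary objective. Equal within-site means could be read as showing that bracelet alerts reach a test as quickly as symptom alerts, when a smaller share of them do so.

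**Working it through.** The protocol gives no expected delay, testing uptake or power for this endpoint, so there is no figure to reproduce. The check is structural, with illustrations on assumed inputs.

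**Structure.** Let the delay distribution within each route be the same in both conditions. Then the expected within-site difference is 0 at the GGD and 0 at the central laboratory, whatever the kit share and whatever the share never tested. Neither quantity enters a within-site mean among testers.

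**Illustration 1 (all inputs assumed).** Mean delay 1.5 days at the GGD and 4 days by kit; gamma distribution with shape 4; kit share 5% in control and 40% in experimental; tested after a red light 70% and 50%.

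- Pooled mean among testers, control: 0.95 × 1.5 + 0.05 × 4 = 1.625 days.
- Pooled mean among testers, experimental: 0.60 × 1.5 + 0.40 × 4 = 2.50 days. Difference 0.875 days.
- Probability of a delay of 3 days or less, given a test: 1 − e^(−x)(1 + x + x²/2 + x³/6), with x = 12/mean. GGD, x = 8: 0.958. Kit, x = 3: 0.353.
- Share of all alerted subjects tested by day 3, control: 0.70 × (0.95 × 0.958 + 0.05 × 0.353) = 64.9%.
- Same share, experimental: 0.50 × (0.60 × 0.958 + 0.40 × 0.353) = 35.8%.

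In 2,000 simulated trials with 1,000 alerted subjects per condition, two-sided t-tests at 0.05 within site rejected in 5.4% (GGD) and 4.8% (central laboratory) of trials, which is chance level. A t-test pooled over sites, and a chi-square test on the share tested by day 3, rejected in every trial.

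Range: with kit means of 3, 4 or 6 days and experimental kit shares of 20%, 40% or 60% (control 5%), the pooled difference is (kit mean − 1.5) × (experimental share − 0.05). It runs from 1.5 × 0.15 = 0.225 days to 4.5 × 0.55 = 2.475 days.

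**Never-tested part alone.** With the kit share at 5% in both conditions and only uptake differing (70% against 50%), the mean delay among testers is identical, pooled or by site. The share tested by day 3 is 64.9% against 0.50 × (0.95 × 0.958 + 0.05 × 0.353) = 46.4%. This part does not require kits to be slower.

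**Illustration 2 (other assumptions).** Exponential delays; symptomatic alerts tested 60% of the time at the GGD, mean 2 days; symptom-free alerts 30% by kit, mean 7 days.

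- Tested by day 5, symptomatic: 0.6 × (1 − e^(−5/2)) = 0.551. Symptom-free: 0.3 × (1 − e^(−5/7)) = 0.153.
- With 20/30/40% of experimental alerts symptom-free, the shares tested by day 5 are 0.8 × 0.551 + 0.2 × 0.153 = 47%, and likewise 43% and 39%, against 55% in control.
- Ever tested: 54/51/48% against 60%.

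Here control has no kit tests, so only the GGD means can be compared, and they are equal.

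**Other planned outputs.** Section 8.1.2 counts GGD tests, kits used and tests due to a red light. Section 10.5 compares test counts by site and the percentage of subjects with a red light. None carries a delay. Section 10.5 takes percentages over all subjects in the condition, so the share of alerted subjects who tested is not produced. Its survival methods are named for other endpoints.

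**The case against.** The best defence is that the protocol as a whole is not blind to either effect. Kits used and tests by site are reported, and Section 10 (general statistical approach) requires the number of observations for continuous variables and the count of known missing data. In illustration 1, per 1,000 alerted subjects, a reader would see 1,000 × 0.70 × 0.05 = 35 kit tests in control against 1,000 × 0.50 × 0.40 = 200 in experimental. In illustration 2 the control kit cell would be empty. That stands: a shift to kits would be visible, and under-testing would show crudely. A reader might infer that these effects can appear nowhere; the documents do not support that. The gap is confined to the delay comparison.

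Further points that stand:

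- The protocol does not say that delays will be reported only within site. Section 10 promises overall results as well as results by stratum, but its example is risk group, and no comparison pooled over test site is stated.
- A reader might take shorter track-and-trace delay to be the trial's main purpose. Section 1 gives that as earlier detection than symptom reporting alone, and reduced delay as something this may help with.
- Asymptomatic close contacts qualify at the GGD, and the criteria may change (Section 3.5). This weakens the route shift without removing it.
- Kit slowness is inferred from the extra steps; no turnaround time is given. Equal within-route delays are a premise of the illustrations, not a prediction.
- Site-specific delay is a sensible logistics summary.

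It can also be said that censoring and denominators belong in the statistical analysis plan. Finer detail does. But the t-test on days, the split by site and the per-route endpoints are choices that this protocol already makes.

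**Conclusion.** The concern holds for the stated comparison of time from red light to test. It rests on testers only and is split on a route that the condition partly determines, so it does not answer an objective about time to testing of the subject. It can show no difference although fewer experimental alerts lead to a timely test.

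The structural result follows from the text. The size does not: testing uptake, kit share and delays are all assumed, and the protocol gives none of them. A reader might infer that bracelet alerts will in fact be tested later or less often. The documents do not show that; they show only that this analysis could miss it.

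Severity is modest. This is one of fifteen secondary objectives, it has no power calculation, and no primary conclusion depends on it.

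**What to change.** For secondary objective 6, make the main analysis the time from a subject's first red light in the period to the first virus test by any route:

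- Include all subjects with a red light in that period.
- Censor untested subjects at period end, and state how withdrawal and death are handled.
- Report the cumulative proportion tested by a fixed day, for example day 5 or 7, per condition, with a log-rank test stratified by risk group.
- Keep the means by site and by test method as description.

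Starting from the first red light agrees with Section 8.1.2 and avoids having to define alert episodes.

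One limit remains. Receiving a red light also depends on the condition, so this comparison is not fully protected by randomisation and should be labelled so. Report beside it, with all randomised subjects as denominator, the proportion who had a red light and were tested within the same window.

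The cost is protocol or analysis-plan wording, a short censoring rule and some programming. The app logs and two-weekly surveys (Sections 8.4.13 and 8.4.14) already collect the data.

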## 10.6 Analysis of Safety

As the Ava bracelet is well-characterized within its marketed indication, we expect very few reports of ADEs and for those to be minor (e.g., skin rash after wearing the Ava bracelet). ADEs will be listed and no statistical summary of these data are planned.

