### 3.8 Additional outcome measures

Additional outcome measures collected outside the Ava COVID-RED app will include:

1. Baseline demographic and risk factors (collected using an online form at subject registration)
2. Epidemiological and infection risk information (collected using bi-weekly online surveys)
3. Self-reported data on time to testing, testing procedures and the results (collected using bi-weekly online surveys)
4. Self-reported data on reception of COVID-19 vaccination (collected using bi-weekly online surveys)
5. Medical event reporting by subjects who have interactions with a general practitioner or a hospital related to SARS-CoV-2 infection, providing healthcare utilization measures during follow-up (collected using bi-weekly online surveys and followed-up by structured phone interviews)
6. Adverse device effects reporting by subjects (collected through the helpdesk [by phone or e-mail] and reminded in monthly online surveys and followed-up by structured phone interviews, if necessary)

See Figure 1 for an overview of the study design described above. See Figure 2 for an illustration of the planning and logistics of the trial as described above. Note that this is a schematic representation and may not fully reflect the exact conduct of the trial.

[figure not shown]

Figure 1: Study design of COVID-RED

[figure not shown]

Figure 2: Schematic illustration of the planning and procedures of the COVID-RED trial

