## 4. STUDY POPULATION

### 4.1 Population (base)

A target of 20,000 subjects will be enrolled in this study. Subjects will initially be recruited from existing cohorts as well as via public campaigns. Members of existing cohorts will be contacted through email or mail to inform them about the COVID-RED study and to invite them to visit the COVID-RED web portal. For the public campaign, a public link will be available for any individual who wants to know more about the study and would like to participate. Subjects visit the COVID-RED web portal where it will be verified if the subject meets the criteria to join the study and information on participation in the study is provided. When the subject is interested to join the study the consent can be given in the portal. More details on the recruitment and consent process are included in section 8 and 11.2.

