#### **8.4.15 Regular completion of hospital episodes and adverse device effects (ADEs)**

Subjects will regularly be asked to self-report possible hospital episodes related to COVID-19 (once every two weeks) and adverse device effects (ADEs) (once every month). For hospital episodes, questions on the dates and name of the facilities will be included.

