### **8.5.1 Specific criteria for withdrawal**

A subject will be withdrawn from the study for any of the following reasons:

- Lost to follow up
- Withdrawal of consent
- Death
- If a subject is poorly compliant (< 20%) with the completion of either the daily Symptom Diary or syncing of the bracelet
- If the subject is using the Ava Bracelet for other purposes as the study purpose (for example for women to detect menstrual cycle changes among ovulation)

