#### *Analysis sets*

Several analysis sets will be defined which will be used for the analyses described in the following sections:

- **Intention-to-treat set:** All subjects randomized to one of the two study sequences. For the analysis, subjects will be considered part of the study sequence that they were originally randomized to. Note that when a subject has their first SARS-CoV-2 infection (as confirmed through a positive PCR/antigen or serology test), they will no longer be part of the analysis going forward because they have met the primary outcome.

- **Efficacy analysis set:** All compliant subjects randomized to one of the two study sequences, where compliance is defined as having entered symptom data in the Ava COVID-RED app on at least 80% of the days of Period 2 **and**, when in the experimental condition, having worn and synchronised the Ava bracelet on at least 80% of the days of Period 2.
- **Partial compliance set:** All subjects randomized to one of the two study sequences that were partially compliant; which is defined as having entered symptom data in the Ava COVID-RED app on at least 80% of the days of Period 2 **or**, when in the experimental condition, having worn and synchronised the Ava bracelet on at least 80% of the days of Period 2.
- **Safety analysis set:** All subjects who were randomized and received an Ava bracelet.

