### 13.2 Synthesis

The risks for the intervention (wearing the Ava bracelet and interaction with the Ava COVID-RED app) are expected to be very minimal. Subjects will be treated with the standard of care and will receive the study intervention on top of their standard care.

Subjects will be instructed to discontinue wearing the Ava bracelet and contact the study team in case they experience any signs of allergic reaction at their wrist, feel soreness, tingling, numbness, burning or stiffness in their hands or wrists while or after wearing the bracelet.

Overall, the burden for the subjects is assessed as small and is justified given the importance of retrieving more information on a potential method in early detection of COVID-19. The expected benefit is large, as the algorithms trained on the obtained data recordings from the Ava bracelet are expected to recognize COVID-19 earlier than clinical symptoms. The latter would allow for earlier isolation and stratification as well as monitoring of COVID-19 affected patients preventing further spread and allowing for appropriate healthcare.

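### Section 10.6 rules out any summary of adverse device effects, so no device-effect rate is planned, the Safety analysis set goes unused, and a crude rate from the listing may be too low

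*Protocol*

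**What the plan says.** **Analysis.** Section 10.6 gives the expectation "we expect very few reports of ADEs and for those to be minor" and concludes "ADEs will be listed and no statistical summary of these data are planned". It cites the bracelet's record within its marketed indication and states no expected rate.

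**Denominator.** The analysis sets in section 10 include a Safety analysis set: "All subjects who were randomized and received an Ava bracelet". Section 4.1 sets the scale: "A target of 20,000 subjects will be enrolled in this study".

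**Collection.** Section 3.8 describes "Adverse device effects reporting by subjects (collected through the helpdesk [by phone or e-mail] and reminded in monthly online surveys". Section 8.4.15 gives the survey frequency: "adverse device effects (ADEs) (once every month". A reported ADE leads to a structured phone interview (8.4.16), entry in the eCRF (9.2.1) and follow-up (9.4).

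**Stopping the bracelet.** Section 13.2 reads "Subjects will be instructed to discontinue wearing the Ava bracelet and contact the study team in case they experience any signs of allergic reaction" and goes on to soreness, tingling, numbness, burning or stiffness. The Summary says the same.

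**Withdrawal.** Section 8.5.1 lists among its reasons: "If a subject is poorly compliant (< 20%) with the completion of either the daily Symptom Diary or syncing of the bracelet". The others are loss to follow-up, withdrawn consent, death and use of the bracelet for other purposes. None is device-related.

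**The concern.** Two things are at issue.

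First, the plan collects device effects from a very large group of wearers, defines the set over which they would be counted, and then states that nothing will be counted. The expectation of few and minor effects is never compared with a number. That matters because recording is restricted to device-related events (9.2.1), there is no DSMB (9.5), and the marketed indication relied on is fertility tracking, whereas this trial enrols adults in general, 7,000 of them planned as high-risk (2 × 3,500).

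Second, anyone who later derives a rate from the listing inherits a possible gap in capture. A subject with wrist symptoms is told to stop wearing the bracelet. Stopping means no syncing, and low syncing is a ground for withdrawal as poorly compliant. If that subject has not contacted the study team, nothing in 8.5, 8.5.1 or 8.4.17 prompts an ADE question at exit, and no reason code would show that the device was the cause.

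**Working it through.** **1. Is the Safety analysis set used?** Sections 10.1 (baseline), 10.3 (time to event) and 10.5 (secondary endpoints) name the Intention-to-treat, Efficacy and Partial compliance sets. Section 10.2 (primary) names the first two. Section 10.6 names no set. The Safety analysis set is therefore assigned to no analysis. The general approach in section 10 presents categorical variables as numbers and percentages; 10.6 departs from this for ADEs.

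**2. What precision is available?** The protocol gives no safety rate, power or precision to reproduce. Only the head count can be checked: 2 sequences × (6,500 + 3,500) = 20,000, which agrees with 4.1. Assume that all 20,000 receive a bracelet and take exact (Clopper-Pearson) two-sided 95% intervals for x/20,000. The event counts are assumptions. With no events the upper limit is 1 − 0.025^(1/20,000) = 0.000184.

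| Subjects with an ADE | Proportion | Exact 95% interval |
|---|---|---|
| 0 | 0% | 0 to 0.018% |
| 20 | 0.1% | 0.061% to 0.154% |
| 100 | 0.5% | 0.41% to 0.61% |
| 200 | 1% | 0.87% to 1.15% |
| 600 | 3% | 2.77% to 3.25% |

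These intervals describe reported ADEs. They measure sampling error only and do not cover under-reporting.

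**3. Can the 20% rule act before the next monthly survey?** Section 8.5.1 states no window, so each reading has to be tried. Assume full wear before the stop and a 30-day survey cycle with stops spread evenly over it.

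*Rolling window of W days.* The rule is met at the smallest number k of unworn days with (W − k)/W < 0.20. The share of stops that reach k before the next survey is (30 − k)/30.

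| W (days) | k (unworn days) | Share before next survey |
|---|---|---|
| 7 | 6 | 80% |
| 14 | 12 | 60% |
| 28 | 23 | 23% |
| 30 | 25 | 17% |
| 37 | 30 | 0% |

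*Cumulative count after D worn days.* The rule is met when D/(D + k) < 0.20. D = 7 needs 29 unworn days, D = 8 needs 33, D = 14 needs 57 and D = 30 needs 121. Only D of 7 or fewer can precede the next survey.

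*The definition in 8.1.2.* The compliance rate there is taken over duration of use, which ends on the last synchronised day. Days after the stop do not enter, so stopping never lowers the rate and never triggers the rule.

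The answer thus runs from none to most stops, depending on a definition that 8.5.1 does not give.

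**4. Illustration of the effect on a crude rate.** Every input here is assumed. Recorded rate = true rate × (1 − s × q × (1 − r)), where s is the share of ADE subjects who stop, q the share of those withdrawn before the survey and no longer surveyed, and r the share of those who contact the study team. With a true rate of 1%, s = 0.5 and q = 0.8:
- r = 0: 1% × (1 − 0.4) = 0.6%
- r = 0.5: 1% × (1 − 0.2) = 0.8%

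Under 8.1.2, q = 0 and nothing is lost by this route.

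**The case against.** The choice of a listing is explained. The hardware is identical to a CE-marked product (6.1, 9.2), and every subject wears it in both conditions, so there is no difference in device exposure to compare. Serious effects do not rest on the listing: they go to the manufacturer within 24 hours, to the authorities on an expedited or quarterly basis (9.2.2), and are always followed up (9.4). This limits the weight of the point. It does not explain why a defined denominator is left without a count.

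Four stronger readings are tempting, and the protocol does not support them.

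- **That no usable rate can be obtained.** The listing supplies a numerator and the Safety analysis set a denominator. What is missing is a planned output.
- **That a subject who stops will be lost before the next survey.** The sentence that tells subjects to stop wearing the bracelet also tells them to contact the study team, and the helpdesk takes reports by phone or e-mail; the monthly survey is a reminder. Withdrawal ahead of the survey needs a short rolling window that 8.5.1 does not state, or a cumulative count after very few worn days. Section 12.1 also mentions physician interviews in lost-to-follow-up scenarios.
- **That the adherence objective (2.2, item 11) is biased.** Non-wear because of intolerance is real non-wear. On the 8.1.2 definition it shortens duration of use, correctly, and leaves the compliance rate unchanged.
- **That a fixed percentage of ADEs goes missing.** The protocol gives no ADE rate, stopping rate or contact rate, so any such figure only restates an assumption.

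What remains is that 8.5.1 has no window, no exception for an instructed stop and no device-related reason.

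**Conclusion.** The point holds in a limited form. Section 10.6 settles the matter in the protocol itself, so it is not something left for the SAP: ADEs are listed, no rate is planned, and the Safety analysis set has no use. At 20,000 wearers the rate given up would be precise (0 to 0.018% with no events; 0.87% to 1.15% at an assumed 1%), provided that all receive a bracelet and reporting is complete.

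A crude proportion can be formed afterwards, but it may be too low, because an unreported device-driven stop may be filed as poor compliance. The size of that loss cannot be determined from the protocol: it is nil on the 8.1.2 definition and could be material under a short rolling window if few affected subjects make contact. This is a modest reporting and coding defect that is nearly free to correct; it is not a failure of safety oversight.

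**What to change.** - **Section 10.6:** replace the exclusion of any summary with the number and percentage of subjects having at least one ADE, SADE, device deficiency and ADE-related stop of bracelet use. Give exact 95% intervals over the Safety analysis set and by risk stratum, and keep the listing.
- **Reason for stopping:** record a device-related stop as its own reason, separate from poor compliance.
- **Withdrawal:** send the existing online ADE survey once when a subject is withdrawn, whatever the reason.
- **Consistency:** reconcile 8.5.1, 8.1.2 and 13.2 on how compliance is measured after a subject stops wearing the bracelet as instructed, including the period over which the 20% is assessed. Which rule applies is for the sponsor to decide.

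The cost is one table, one reason code and one extra send of an existing survey. The small downside is some additional follow-up interviews under 8.4.16, since each newly reported ADE triggers a call.
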